### *5.3 The type and timing of the data to be collected for withdrawn subjects.*

Vital status and hospitalization at 30-days post hospital discharge

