## 7.2 Methods and timing for assessing, recording, and analysing efficacy parameters.

Post-discharge interviews will be performed by trained research staff and will use a standardized questionnaire to obtain the information necessary to help determine if an adverse event has occurred and obtain an estimate of the patient's sleep quality and post-discharge health-related quality of life.

These post-discharge surveys will be combined with patient demographics into a de-identified record as soon as the telephone interview has been completed. Trained adjudicators will review these records and determine if an adverse (drug) event occurred post-discharge.

We will also, with consent, collect data on prescribed medications, hospitalizations and medical services that any eligible participant receives 12 months prior to their enrolment in the study, during their hospital admission at the time of enrolment, and up to 12 months after their hospital admission. Subsequently, when sufficient funding is available and/or provincial access pathways are clarified we will perform a pre-planned secondary analysis on those with long-term administrative data.

Patients will have the option of consenting for both the telephone interview and access to medication and hospitalization data for up to 1-year post-discharge, data access only, or interview only.

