## Section 9 – Statistics/Statistical Analysis Plan

### 9.1a *A description of the statistical methods to be employed, including timing of any planned interim analysis(es).*

Baseline characteristics will be expressed as numbers and percentages for categorical variables and median and interquartile range (IQR) for continuous variables. Differences between control and intervention baseline characteristics will be compared by chi-square or rank-sum as appropriate (for descriptive purposes since this is a cluster randomized trial and there may be chance imbalances due to case-mix during the intervention and control periods).

All analysis will be by intention to treat except where otherwise noted.

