#### Primary Outcome - Adverse Drug Events

A mixed-effects logistic regression model will be used for the outcome of adverse drug events ( $\geq 5$  on Leape-Bates scale) which controls for intervention, time period, and number of baseline potentially inappropriate medications as fixed effects and cluster as a random effect. This model will be used to estimate adjusted risk differences.

A sensitivity analysis will be conducted (supplemental) using a Leape-Bates Scale of  $\geq 4$  for the definition of adverse drug events.

This analysis will be conducted on patients who have consented to, and participated in, the post-discharge follow-up.

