### *9.5 Procedure for accounting for missing, unused, and spurious data.*

Significant attempts will be made to have complete data. In the event of missing data, complete case analysis or multiple imputation will be performed as are appropriate to the situation.

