### *9.7 The selection of subjects to be included in the analyses (e.g., all randomized subjects, all dosed subjects, all eligible subjects, evaluable subjects).*

All subjects who consent and receive a deprescribing report while in hospital and who survive to hospital discharge will be analyzed for the primary outcome (which occurs within 30-days of hospital discharge). Subjects who die in hospital will not be analyzed for the primary outcome as they cannot experience the primary outcome.

For measures of efficacy on deprescribing at discharge, the population of interest will be all subjects who have 1 or more potentially inappropriate medication identified at baseline and who

1073 are discharged alive from a study unit regardless of whether or not they complete the post-  
1074 discharge interview.  
1075  
1076

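### Sections 9.1a and 9.7 define the primary ADE population differently, and no listed analysis tests the loss of patients without post-discharge follow-up

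*Protocol*

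**What the plan says.** Section 9.1a sets a general rule, "All analysis will be by intention to treat except where otherwise noted", and then limits the primary ADE model: "This analysis will be conducted on patients who have consented to, and participated in, the post-discharge follow-up".

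Section 9.7, which selects the subjects for each analysis, reads differently: "All subjects who consent and receive a deprescribing report while in hospital and who survive to hospital discharge will be analyzed for the primary outcome". It names only in-hospital deaths as excluded. For deprescribing at discharge it keeps patients "regardless of whether or not they complete" the interview, so enrolled patients without one are expected.

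Other sections show where such patients come from:
- Section 7.2 lets patients choose both the interview and data access, "data access only, or interview only".
- Section 12 seeks a consent waiver for the intervention where a province allows it, with consent for the interview sought separately.
- Sections 5.2 to 5.5 end follow-up on withdrawal. What is then sought is "Vital status and hospitalization at 30-days post hospital discharge", plus ER visits, through a short call if the patient agrees.

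On missing data, section 9.5 says: "In the event of missing data, complete case analysis or multiple imputation will be performed as are appropriate to the situation". The planned sensitivity analysis of the primary outcome lowers the Leape-Bates cut-off to 4. The five post-hoc analyses in 9.1b concern the small number of clusters and patient factors that differ between groups.

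**The concern.** Two statements about who is in the primary analysis cannot both be applied as written. Section 9.1a makes participation after discharge a condition of entry. Section 9.7 does not, but it requires receipt of a report, and section 2.2 says no prioritized deprescribing list is generated for patients in the control period. Taken literally, 9.7 leaves no control patients.

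If 9.1a governs, the analysis conditions on something that happens after exposure. Participation could be related to phase: section 4.3(b) conceals the objectives in the control phase and cannot do so in the intervention phase, and section 2.2 gives a brochure to intervention-phase patients who consent to follow-up. For patients who withdraw or are not reached, it could also be related to the outcome.

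The primary model adjusts for intervention, period and baseline PIM count. It would not absorb a participation difference that runs through ADE status itself, or through a prognostic factor such as frailty. Every listed ADE analysis that states its population uses participants only, so a distortion would not show.

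**Working it through.** **Inputs from section 9.2 (revised design).** 3 clusters × 4 periods × 500 = 6000 patients; control ADE risk 15%; detectable difference 4.8 points, so intervention risk 15 − 4.8 = 10.2%; 1/0.048 = 20.8, matching the stated NNT of 21. The Hussey and Hughes variance with control-rate variance and two-sided alpha 0.05 gives power of 79.9%, 79.9% and 80.6% at ICC 0.01, 0.03 and 0.05. The stated 80% therefore reproduces, with all 6000 analysed. The implied standard error is about 4.8/(1.96 + 0.84) = 1.7 points.

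**Assumed inputs.** The protocol gives no non-participation rate. Let m0 be the share missed among patients without an ADE, and m1 = ratio × m0 the share missed among those with one.

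**Formula.** Risk among participants = p(1 − m1) / [p(1 − m1) + (1 − p)(1 − m0)].

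Example, both phases, m0 = 15%, ratio 2 (m1 = 30%):
- Control: 0.15 × 0.70 / (0.15 × 0.70 + 0.85 × 0.85) = 0.1050/0.8275 = 12.69%.
- Intervention: 0.102 × 0.70 / (0.102 × 0.70 + 0.898 × 0.85) = 0.0714/0.8347 = 8.55%.
- Difference: 4.13 points (from unrounded risks).

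| Assumed loss | Control % | Intervention % | Difference (points) | Odds ratio |
|---|---|---|---|---|
| None | 15.00 | 10.20 | 4.80 | 0.644 |
| Both phases, 10%, ratio 2 | 13.56 | 9.17 | 4.39 | 0.644 |
| Both phases, 20%, ratio 1.5 | 13.38 | 9.04 | 4.34 | 0.644 |
| Both phases, 15%, ratio 2 | 12.69 | 8.55 | 4.13 | 0.644 |
| Both phases, 20%, ratio 2 | 11.69 | 7.85 | 3.84 | 0.644 |
| Intervention only, 10%, ratio 1.5 | 15.00 | 9.69 | 5.31 | 0.608 |
| Control only, 10%, ratio 1.5 | 14.29 | 10.20 | 4.09 | 0.682 |

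With equal loss, (1 − m1)/(1 − m0) multiplies the odds in both phases and cancels from the odds ratio. Only the absolute scale shrinks, and the protocol reports adjusted risk differences. With loss in one phase it does not cancel: 0.644 × 0.85/0.90 = 0.608, and 0.644 × 0.90/0.85 = 0.682. The shifts are 5.31 − 4.80 = 0.51 and 4.80 − 4.09 = 0.71 points, or 0.30 and 0.42 of a 1.7-point standard error.

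**Under no true effect.** Suppose the risk is 15% in both phases and 85% take part, except that intervention-phase patients with an ADE take part 10 points less often (75%). The intervention risk then reads 0.15 × 0.75 / (0.15 × 0.75 + 0.85 × 0.85) = 0.1125/0.835 = 13.5%, an apparent benefit of 1.5 points.

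**The case against.** The strongest reply has four parts.

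**Section 9.7 already has the wider population.** One could read 9.7 as the population and 9.1a as the complete-case analysis within it. A reader might infer from 9.1a alone that the imputation in 9.5 can never reach non-participants. Section 9.7 does not support that, since under its wording they are in the set and 9.5 could apply. But the protocol does not say that the two sections are layered in this way, and the report condition in 9.7 fails for controls. The contradiction stands.

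**The protocol limits the loss.** Next of kin are interviewed after out-of-hospital deaths (7.1), readmitted patients have a short-form interview (7.3, Adjudication Manual), and patients expected to be unreachable by telephone are excluded (5.1.b). A reader might suppose that readmitted patients are the ones lost; the short-form interview points the other way. Consent is taken on days 1 to 3 (4.4), so a choice of data access only cannot result from a later ADE, although it could differ by phase or prognosis. These points stand. They leave withdrawn and unreached patients, and ADEs that do not lead to readmission.

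**Equal loss does not harm the test.** This is correct: the odds ratio is unchanged, and a complete-case logistic model is valid when participation depends only on modelled covariates. The comparison is distorted when the dependence on ADE status differs between phases, or when participation runs through unmodelled prognosis.

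**Imputation may gain little.** When loss depends on ADE status itself, missing-at-random imputation would roughly return the participants-only estimate. A reader might hope that imputing from readmission status restores the full 4.8 points. That needs the status of every missed patient, whereas the 30-day status call covers only withdrawn patients who agree, and the administrative data in 7.2 await funding and provincial access. So there is no firm case for making imputation primary. The case for a delta analysis is unaffected. Details of the imputation model could sit in a separate SAP, but the conflict between 9.1a and 9.7 is in the protocol itself.

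**Conclusion.** The point holds in a limited form. The protocol gives two incompatible primary populations, one of which cannot be applied to controls. The version attached to the primary model drops patients without follow-up, and no listed analysis checks the consequence.

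The size rests on assumed rates. A 4.8-point difference becomes about 3.8 to 4.4 points under equal ADE-dependent loss, with the odds ratio intact, and 5.3 or 4.1 points under the modest one-phase loss examined. The one-phase shifts are less than half of the planned standard error. Larger gaps between phases would matter more, and in the example above they produce a difference where none exists.

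It would go too far to conclude that the primary estimate is biased or that the participants-only model must be replaced. The documents show that participation can depend on phase and outcome; they do not show that it does, or by how much.

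**What to change.** 1. **One population.** Reconcile 9.1a and 9.7: the primary ADE population is all enrolled patients discharged alive, in both phases, with no report-receipt condition for controls. If the participants-only model stays primary, which is acceptable, call it the complete-case analysis of that population.
2. **Participation.** Report the number and proportion with adjudicable follow-up by phase and period, separating withdrawal, not reached, and no consent to interview.
3. **Sensitivity analysis.** In 9.1a and 9.5, replace the open choice for the primary outcome with multiple imputation of ADE status, done separately by phase, from data already collected: baseline characteristics, discharge medications, and 30-day death and ER or hospital status where known. Add a delta (tipping-point) analysis that shifts the imputed ADE risk separately in each phase and reports the shifts at which the conclusion changes.

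Section 9.1b is written in the past tense. If the primary results are already known, label these additions post hoc, as that section does for its own.

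The cost is protocol wording and some programming, with no new patients, visits or adjudications. The drawback is that the imputation will be weak where 30-day status is unknown, so the delta results should carry most of the interpretation.

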#### Secondary Outcome(s)

##### - All adverse events within 30-days post discharge

A mixed-effects logistic regression model will be used for the outcome of adverse events (whether or not ADE-related) which controls for intervention, time period, and number of baseline potentially inappropriate medications as fixed effects and cluster as a random effect. This model will be used to estimate adjusted risk differences. This analysis will be conducted on patients who have consented to, and participated in, the post-discharge follow-up.

##### - Adverse drug withdrawal events within 30-days post discharge

As these are expected to be a rare subset of adverse events, we will provide a comparison of the number of these events in the control and the intervention and the proportion they represent of total adverse drug events. There will be no statistical comparison. This analysis will be conducted on patients who have consented to, and participated in, the post-discharge follow-up.

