#### *2.4 Summary of known potential risks and benefits:*

Few studies have specifically looked for safety events related to deprescribing or “adverse drug withdrawal event” (ADWEs). Most studies of deprescribing have been underpowered to detect an impact on ADEs. This study will add important data to the generation of evidence in favour of deprescribing in acute care from a safety and efficacy point of view. Potential benefits include a reduction in pill burden, direct and indirect medication related costs, improved quality of life, and a reduction in adverse drug events. Potential harms include ADWEs (e.g., seizure after abrupt discontinuation of a benzodiazepine or gastrointestinal bleeding following cessation of a proton pump inhibitor).

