### **Section 3: Trial Objectives and Purpose (general statement)**

Primary objective and secondary objectives: Deliver to the treating team a deprescribing opportunities report prior to the participant's hospital discharge to facilitate deprescribing. It is hypothesized that the intervention will lead to a reduction in Adverse Drug Events within 30 days post-discharge through the cessation of PIMs. Secondary outcomes will include adverse events at 30 days post hospital discharge as well as number of other measures listed subsequently.

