## Section 4: Trial Design

*4.1 A specific statement of the primary endpoints and the secondary endpoints, if any, to be measured during the trial.*

*Primary outcome:* Any adverse drug event within 30-days of hospital discharge (as defined by a 5 or 6 on the Leape and Bates scale). ADEs could include adverse drug withdrawal events (ADWEs).

*Secondary outcomes:*

- Proportion of patients with one or more PIM discontinued at discharge
- Absolute number of medications at discharge
- Absolute number of PIMs at discharge
- Adverse drug withdrawal events within 30-days post discharge
- Absolute number of medications at 30 days post-discharge
  - Proportion of medications that remain deprescribed at 30 days post-discharge
- Adverse events within 30-days post discharge
  - 30-day readmissions (ER or hospitalization) within 30-days post discharge
  - 30-day mortality in those that survive to hospital discharge
  - Falls within 30-days of hospital discharge
- 30-day post-discharge sleep questionnaire responses
- 30-day self-reported health-related quality of life

*Sensitivity analyses:*

- Adverse drug events as defined by a 4,5 or 6 on the Leape and Bates scale

*Effect by:*

- Biological sex
- Admission from a long-term care home
- Palliative status
- Frailty status (dichotomized as moderate to severely frail vs not)

*4.2 A description of the type/design of trial to be conducted (e.g., double-blind, placebo-controlled, parallel design) and a schematic diagram of trial design, procedures, and stages.*

This is a cluster randomized trial comprising 3 clusters: Quebec, Ontario, and Western Canada (Alberta and British Columbia).

*4.3 A description of the measures taken to minimize/avoid bias, including:*

(a) Randomization

The order that the cluster enters intervention is randomized prior to the start of the study.

(b) Blinding and Allocation Concealment

Study sites will only learn that they are crossing over to the intervention 4 weeks prior.

Healthcare personnel and patients at participating sites will remain blinded to the specific objectives of the study while in the control phase. They will be aware that we are conducting a study of post-discharge adverse events; however, they will not know that we are specifically looking at medication appropriateness, deprescribing, and adverse drug events. When study sites cross into intervention it will no longer be possible to blind them to the objectives.

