## Section 8 – Assessment of Safety

### *8.1 Specification of safety parameters*

During adverse drug event adjudication, adverse drug events due to withdrawal of a drug (stopping, tapering, holding, accidental failure to represcribe or deprescribing) are captured in the case report form. Any adverse drug event that is from deprescribing will be reported as a secondary outcome (adverse drug withdrawal events).

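### Withdrawal events, the named harm of deprescribing, are summarised as counts and as a share of all ADEs; that share moves with the primary outcome and is not a risk, and no risk difference or interval is planned.

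*Protocol*

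**What the plan says.** Protocol section 9.1a, under the ADWE heading, fixes the summary as "the number of these events in the control and the intervention and the proportion they represent of total adverse drug events". The reason given is rarity ("As these are expected to be a rare subset of adverse events"), and the text adds "There will be no statistical comparison". The analysis population is patients who agreed to and took part in post-discharge follow-up, the same as for the primary outcome.

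Four other places bear on this:

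- Section 2.4 says "Few studies have specifically looked for safety events related to deprescribing" and "Potential harms include ADWEs". It names no other harm.
- Section 8.1 makes these events the safety parameter: "Any adverse drug event that is from deprescribing will be reported as a secondary outcome (adverse drug withdrawal events").
- Section 4.1 puts them inside the primary outcome: "ADEs could include adverse drug withdrawal events (ADWEs"). Section 3 states the expected direction of that outcome: "It is hypothesized that the intervention will lead to a reduction in Adverse Drug Events within 30 days post-discharge".
- Section 9.1a gives the primary outcome a mixed model and an adjusted risk difference.

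**The concern.** A share of total ADEs answers the question of what proportion of the ADEs that occurred were due to withdrawal. The safety question is how many followed-up patients had a withdrawal event in each phase, and by how much the phases differ. The two answers agree only if total ADE risk is the same in both phases, and the trial is designed on the hypothesis that it is not.

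If the tool works as intended, the share rises even when no additional patient is harmed by withdrawal. If ADEs rose instead, the share could stay flat while withdrawal risk went up.

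Benefit is therefore to be reported as a risk difference, while the one named harm is to be reported as a count and a ratio with a treatment-dependent denominator. Section 2.4 offers the trial as safety evidence on deprescribing, so the size of any excess and its uncertainty are what a reader will look for. Because section 9.1a itself chooses this metric, the point is not a detail left to a separate analysis plan.

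**Working it through.** **Inputs from the Protocol (section 9.2, revised sample size).** 3 clusters, 1 baseline and 3 randomised periods, 500 patients per cluster-period; control ADE rate 15%; detectable absolute difference 4.8 points; NNT 21; at least 80% power; alpha 0.05; ICC 0.01 to 0.05. The Protocol gives no ADWE rate.

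**Assumptions.** One cluster crosses over at each step. Every planned patient is followed up. ADWE risk is taken over a range of 0.5% to 3%. ADEs and ADWEs are counted per patient, since the adjudication form in section 7.3 gives one ADE score and one withdrawal answer per file.

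**Step 1: reproduce the design.** 3 × 4 × 500 = 6000. 15% − 4.8 points = 10.2%. 1/0.048 = 20.8, so NNT 21. With the Hussey and Hughes variance and two-sided alpha 0.05, power for 15% against 10.2% is 84% to 86% using the averaged or pooled binomial variance, and 79% to 81% using the control-arm variance, over ICC 0.01 to 0.05. The stated 80% is reproduced to within about a point or better.

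**Step 2: patients per phase.** Control/intervention by period: 1500/0, 1000/500, 500/1000, 0/1500. That makes 3000 control and 3000 intervention.

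**Step 3: the planned share when withdrawal risk does not change.** Expected ADEs: 3000 × 0.15 = 450 in control and 3000 × 0.102 = 306 under intervention. Share = ADWE patients / ADE patients.

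| Assumed ADWE risk, both phases | ADWEs per phase | Share, control (/450) | Share, intervention (/306) | True risk difference |
|---|---|---|---|---|
| 0.5% | 15 | 3.3% | 4.9% | 0 |
| 1% | 30 | 6.7% | 9.8% | 0 |
| 2% | 60 | 13.3% | 19.6% | 0 |
| 3% | 90 | 20.0% | 29.4% | 0 |

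The ratio of shares is (w/0.102)/(w/0.15) = 0.15/0.102 = 1.47 for any ADWE risk w. It depends neither on the assumed ADWE risk nor on the 3000 per phase.

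**Step 4: what an unchanged share would mean.** At the design effect, equal shares require the ADWE risk to fall by 1 − 0.102/0.15 = 32%, for example from 1.0% to 0.68%. Conversely, if ADEs rose from 15% to 18%, a rise in ADWE risk from 1.0% to 1.2% would leave the share at 0.010/0.15 = 0.012/0.18 = 6.7% in both phases.

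**Step 5: what an interval would offer.** With 30 events in 3000 in each phase, the unadjusted 95% half-width is 1.96 × √(2 × 0.01 × 0.99/3000) = 0.50 points. With the Hussey and Hughes adjustment for period and cluster at ICC 0.03 it is about 0.95 points. Both are normal approximations.

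**The case against.** The best defence is that the plan is open about a rare outcome and describes it modestly.

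- **A comparison is planned.** A reader might infer that the phases will not be compared at all. The text does not support that: it promises a descriptive comparison of counts and excludes only a statistical one.
- **Crude risks can be recovered.** A reader might infer that the trial could say nothing about whether withdrawal harm changed or how large an excess is excluded. That goes too far. The analysis population is named and is the same as for the primary outcome, so a crude risk follows once the numbers followed are reported.
- **Withdrawal harm also enters modelled outcomes.** ADWEs can count in the primary outcome, and all adverse events get their own adjusted risk difference. ER visits or readmissions, deaths and falls are modelled too. None of these isolates withdrawal risk.
- **The share does not flatter the intervention at the design effect.** It makes the intervention look worse, and the counts stand beside it. Hiding a rise in risk requires total ADEs to go up, against the hypothesis, and the primary analysis would show that.
- **Rarity is a fair reason not to test.** With three clusters and few events, any adjusted model is approximate. In step 5 the adjusted half-width is nearly as large as the assumed 1% risk.

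All of this stands, and it narrows the point. Two things remain. A crude risk that a reader has to derive is not one the plan commits to report; it is also unadjusted for period, although intervention patients sit in later periods. And rarity justifies omitting a test, but it does not justify a denominator that treatment changes or the absence of any interval.

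**Conclusion.** The point holds as a poorly chosen summary measure for the one harm the Protocol names. The trial still yields evidence on withdrawal harm, and the primary analysis is unaffected. The planned share is not comparable between phases: at the design effect it is inflated by a factor of 1.47 with no change in withdrawal risk. That factor rests only on the Protocol's 15% and 10.2%. The individual shares rest on assumed ADWE risks, and the event counts and interval widths also rest on 3000 followed per phase, which is optimistic because section 7.2 lets patients consent to data access without the interview. What is missing is a committed per-patient risk and a risk difference with an interval. It should be added, because it is cheap and goes to the safety evidence that section 2.4 offers.

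**What to change.** In the ADWE paragraph of section 9.1a:

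1. Report, for each phase, the number and percentage of followed-up patients with at least one ADWE, with the number followed as denominator.
2. Report the risk difference between phases with a 95% CI, as estimation only and without a test.
3. Where event numbers allow, adjust for period and cluster with a sparse-data method (Firth-penalised logistic regression is one option), and state that the interval is approximate with three clusters. Otherwise give the unadjusted difference and label it as not adjusted for period or cluster.
4. Keep the share of ADEs only as a description of the make-up of the primary outcome, and say that it is not a measure of withdrawal risk.

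No new data are needed, because section 7.3 already has adjudicators record whether each ADE was related to withdrawal. The cost is a few sentences of analysis wording and a little more analysis work. The downside is that the intervals will be wide and approximate, and the report should say so.
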